### 2.4. Statistical Analysis

The primary outcome will be changes in the levels of students’ motivation for out-of-school PA. Secondarily, perceived exercise autonomy support, the intention to be physically active, perception of PA levels, engagement in PE and academic performance will also be assessed. For this purpose, firstly, the nature of the variables will be taken into account through the application of normality, validity, and reliability tests. Secondly, the principles of independence, normality, linearity and variance of the study variables will be tested for general linear model analyses. Thirdly, intergroup and intragroup differences will be analysed with repeated-measures ANOVA or nonparametric tests such as McNemar’s or the Kruskall–Wallis tests, as appropriate. For continuous variables, Bonferroni-corrected multiple paired *t*-tests will be calculated to determine intra-group (i.e., between the experimental and control group) and inter-group (i.e., between the pre-test and post-test) differences. For categorical variables, a chi-square test will be performed. While Cramer’s V will be used to describe the degree of association between categorical variables and experimental and control schools, McNemar’s test will be used to analyse baseline and post-intervention differences in categorical variables in experimental and control schools, respectively. Effect sizes will be assessed using Partial Eta Squared (η_p_^2^) and Cramer’s V values for continuous and categorical variables, respectively. Effect sizes will be considered small, moderate or large when η_p_^2^ is greater than 0.01, 0.06 and 0.14, respectively, and when Cramer’s V is greater than 0.10, 0.30 and 0.50, respectively. Significance will be set at *p* < 0.05 for all analyses.

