## Abstract

Low levels of physical activity (PA) are a concern among students, producing negative physical, health and mental consequences. This study aims to present a protocol intervention in physical education (PE) based on self-determination theory (SDT) to enhance students’ motivation towards performing PA and increasing their PA levels in their leisure time. This protocol is a convenience study with two allocation arms (intervention group versus control group). SDT-based motivational strategies will be carried out and co-created with PE teachers to increase motivation and out-of-school PA levels. Data collection will be conducted three times: before the intervention, after the intervention (four months after baseline) and at the end of the intervention (retention measurement, seven months after baseline). The measures will assess perceived teacher support for PA, motivation towards PA, intention to be physically active, PA levels, engagement in PE and academic performance. Overall, this intervention programme is expected to increase students’ autonomous motivation for PA and their PA levels in their free time. This intervention might encourage teachers to establish strategies and resources to increase their students’ adaptive outcomes.

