### 2.2. Intervention Based on SDT in Primary School

In February, an informative document will also be given to the families or legal guardians, accompanied by the informed consent to be signed. The research team will go to the schools to collect the data on certain days according to the organisational availability of the teachers during lessons. There will always be at least one research team member in the classroom while the students complete the questionnaires to solve any possible doubts. The questionnaires will be completed on paper in approximately 40 min. The variables described in Section 2.3 will be measured three times: (i) before the intervention (February); (ii) after the intervention (June); and (iii) a follow-up measure at the beginning of the following school year under the same conditions as in the two previous measures (October).

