*Motivation for Physical Activity.* To assess motivation to practice physical-sports activity, an adaptation of the Behavioural Regulation in Exercise Questionnaire (BREQ-3; [48]), validated for the Spanish context by González-Cutre et al. [49], will be used. This scale begins with stem “I exercise because…”, followed by 23 items, grouped into six factors that measure intrinsic motivation (i.e., “it’s fun and satisfying to exercise”), integrated regulation (i.e., “it is consistent with my lifegoals”), identified regulation (i.e., “I think it’s important to make the effort to exercise regularly”), introjected regulation (i.e., “I feel a failure when I haven’t exercised in a while”), external regulation (i.e., “I feel under pressure from friends/family to exercise”), and amotivation (i.e., “I think exercise is a waste of time”). All the factors have four items except for the identified regulation, which has three. The response format is a Likert scale ranging from 1 (totally disagree) to 5 (totally agree).

*Intention to be Physically Active.* We used the Intention to be Physically Active (MIFA) questionnaire, created by Hein et al. [50] and adapted to the Spanish context by Moreno-Murcia et al. [51]. This instrument was developed with Spanish primary school students [52]. The scale is preceded by the phrase, “Regarding your intention to take up a sporting activity ...”, and comprises 5 items (i.e., “I am interested in developing my physical fitness”). The response format is a Likert scale ranging from 1 (totally disagree) to 5 (totally agree).

*Perception of Physical Activity Levels.* The Spanish-validated scale of Benítez-Porres et al. [53] was used to assess PA in children. This self-administered questionnaire measures moderate to vigorous PA performed in the last seven days in students. It consists of ten items, nine of which are used to calculate the activity level. The other item assesses whether any illness or other event prevented the child from doing their regular activities in the last week. The items are scored from 1 to 5.

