## 4. Conclusions

It is expected that these school-based interventions aimed to promote the PA practice in the leisure time of students’ primary school will have positive consequences on them, such as increasing the levels of intrinsic motivation, increasing engagement during PE classes, reducing controlled motivation and demotivation towards PE and towards the practice of PA, and, consequently, there will be a positive predisposition towards the intention to carry out PA and increase the levels of PA practice of the students.

Regarding the first limitation that we can find in the development of the intervention, the need to have a supervisor in order to control the compliance and development of the strategies developed by the teachers may be a factor that may hinder the replication of similar interventions. Therefore, researchers who wish to carry out a similar intervention are urged to take into account the need or not to include an agent who can supervise the intervention to be carried out.

On the other hand, another of the limitations that can be found is due to the possible curricular modifications that the intervention may undergo as a result of the continuous legislative modifications in the educational context. Furthermore, it is important to highlight that each school has a different educational reality (i.e., the different organisation of the centre, practice spaces, quantity of PE teachers and students), and therefore, the strategies to be developed must be adapted and can be developed differently in the schools of the intervention programme.

Finally, taking into account the educational reality of PE teachers, it is important to emphasise that the teachers in this research have the theoretical and practical support of a research team. For this reason, it is encouraged to encourage PE teachers that if they do not have similar support behind them, they should carry out autonomous learning and training in motivational theories such as SDT in order to improve the teaching-learning process of their students.

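### The primary outcome is not tied to one BREQ-3 score or one time point, and the stated Bonferroni correction is not said to cover the six factors

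*Protocol article*

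**What the plan says.** Section 2.4 (Statistical Analysis) states: "The primary outcome will be changes in the levels of students’ motivation for out-of-school PA". It names no score, contrast or assessment time.

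Section 2.3 (Measures) assesses motivation with an adaptation of BREQ-3, in which the stem is "followed by 23 items, grouped into six factors": intrinsic motivation, integrated, identified, introjected and external regulation, and amotivation. No total or index is described. Sections 2.2 and 2.3 place assessments in February, June and October, so two of the three follow baseline.

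For the analysis, Section 2.4 says that "intergroup and intragroup differences will be analysed with repeated-measures ANOVA or nonparametric tests". It adds Bonferroni-corrected paired t-tests for differences between groups and between pre-test and post-test, and sets the error level thus: "Significance will be set at *p* < 0.05 for all analyses".

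The expected effect is worded in two places. The Abstract says the programme is "expected to increase students’ autonomous motivation for PA". Section 4 (Conclusions) expects effects such as "increasing the levels of intrinsic motivation", together with less controlled motivation and less demotivation. Section 1.1 groups the regulations into three types (autonomous, controlled, amotivation), but neither Section 2.3 nor Section 2.4 uses that grouping.

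**The concern.** BREQ-3 as described has no single level of motivation that could change. The intervention is meant to raise some of the six scores and lower others, so they cannot simply be read as one quantity. A primary outcome worded as change in motivation can therefore be met by several different results, and the article does not say which one decides the question or at which assessment.

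The error rule does not close the gap. The 0.05 level applies analysis by analysis. The one stated correction concerns paired comparisons between groups and between times, and nothing extends it across the factors. If an analyst tests each factor and reports a significant one as the primary result, the nominal 5% no longer describes the risk of a false primary claim. A reader of the published plan also could not tell whether the reported score was chosen before the data were seen.

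**Working it through.** The plan states no familywise error rate, so it has no figure of its own to reproduce here.

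**Inputs from the protocol article**
- Scores available for the primary outcome: 6 (Section 2.3).
- Level: 0.05 per analysis (Section 2.4). Sidedness is not stated; two-sided is assumed.
- Main test: repeated-measures ANOVA, which can cover all assessment times in one omnibus test per score (Section 2.4). This gives about six tests, one per factor.
- Alternative grouping: 3 types of motivation (Section 1.1).

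**Inputs assumed**
- Correlation between the factors' test statistics: 0 (independence), then 0.3 to 0.7. The article gives none.
- Each test on its own holds its 5% level.

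**Step 1. Six factors, one test each, independent.** 1 - (1 - 0.05)^6 = 1 - 0.735 = 0.265, or 26.5%.

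**Step 2. Six factors, correlated.** Simulation of six equally correlated two-sided z-tests, 400,000 draws, standing in for one test per factor:

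| Correlation | At least one p < 0.05 |
|---|---|
| 0.3 | 24% |
| 0.5 | 21% |
| 0.7 | 16% |

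**Step 3. Favourable direction only.** If only a change in the hoped-for direction would be claimed as success, each two-sided 5% comparison contributes 2.5%: 1 - (1 - 0.025)^6 = 1 - 0.859 = 0.141, about 14% if independent. Positive correlation between tests in the favourable direction would lower it.

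**Step 4. Three types instead of six factors.** 1 - (1 - 0.05)^3 = 1 - 0.857 = 0.143, or 14.3% two-sided if independent.

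**Step 5. What the stated Bonferroni correction does.** Applied within a factor, across its group and time comparisons, it holds that factor at about 5%. It does not act between factors, so the six-factor figures stay close to those in Steps 1 and 2.

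**Step 6. After a fix.** One score at one time: 5%. Six factors at 0.05/6 = 0.0083 each: 1 - (1 - 0.0083)^6 = 0.049, or 4.9% if independent; Bonferroni keeps it at or below 5% under any correlation.

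**The case against.** The strongest reply is that the article names one construct, is a condensed account, and may leave scoring and multiplicity rules to a fuller plan that is not shown. That stands for scoring detail. It does not dispose of the point, because the article itself states the primary outcome and a blanket significance rule, and the two together do not identify one primary test.

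Four stronger readings are tempting but not supported:

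- **Any one factor suffices.** A reader might infer that success on any single factor counts. The article never says so, and never declares six separate primary outcomes. It leaves the matter open.
- **Twelve unadjusted tests.** A reader might multiply six factors by two post-baseline times. Repeated-measures ANOVA can cover the times in one test, and the Bonferroni correction most naturally applies to the comparisons that follow. The text also leans towards June: October is called a retention or follow-up measurement, and the contrasts spelled out are pre-test with post-test. One omnibus test per factor is the fairer count.
- **Abstract against Conclusions.** A reader might see a contradiction. Section 1.1 places intrinsic regulation within autonomous motivation, and controlled motivation and amotivation are its other two types. The expectations are compatible. They also state hoped-for directions in advance, which is why Steps 3 and 4 belong in the range.
- **A positive result is likely by chance alone.** Every figure above is well below 50%. The supported statement is that the risk is well above the nominal 5%.

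**Conclusion.** The point holds in this form: the primary outcome is not reduced to one BREQ-3 score or one assessment time, and the stated multiplicity correction is not said to reach across the six factors. If each factor could support the primary claim, the false-positive risk is 26.5% under independence and about 16-24% at correlations of 0.3-0.7. Under independence the milder readings give about 14%: favourable direction only, or the three-type grouping two-sided. These figures rest on one test per factor at 0.05, on correlations that the article does not supply, and on each test holding its own level. The point should be settled before analysis. It is a matter of definition and does not call for a change of design.

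**What to change.** Name one primary outcome in Section 2.4: the autonomous-motivation score, made up of intrinsic, integrated and identified regulation as grouped in Section 1.1. Compare it between experimental and control groups at the June post-test, adjusted for baseline, at two-sided 5%. Section 1.1 gives the grouping but no scoring rule, so fix one in advance, for example the mean of the three regulation scores. This choice matches the expectation in the Abstract.

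Make controlled motivation, amotivation and the October scores secondary, with a stated multiplicity correction such as Holm. Report the individual factors as supportive.

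If the investigators prefer to keep all six factors as primary, they should say so, fix the assessment time, and test each factor at 0.05/6 = 0.0083.

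The change is to wording only. The cost is that the other factor scores lose primary status or, under the alternative, that each factor is tested at a stricter level.

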## 2. Methods

### 2.1. Design and Participants

This quasi-experimental study will be carried out in Cáceres (Extremadura, Spain). Convenience sampling will be conducted in six different Primary Schools. Three schools will be randomly assigned to the control school and the other three schools to the experimental school. The sample size will be estimated using the following formula: *n* = (Z)^2^ (*p*(1 − *p*) e^2^), where “*n*” is the sample size, Z = 1.96 (95% confidence interval), *p* = number of 4th and 5th primary school students in the city where the study will be conducted (±3350 students), and e = margin of error (3%). The minimum sample size (considering a 10% non-response) will be 345 students. All the schools will have similar socio-demographic and built-environment characteristics [37]. School courses in Extremadura run from early September to mid-June, with a Christmas break from late December to early January and a break around March or April for the Easter holidays. As seen in Figure 1, assessments will be completed at baseline at the beginning of the school course (Term 1, February) and after the intervention (Term 2, June). A follow-up measurement will be conducted at the beginning of the following school course (Term 3, October). The study has been agreed upon by the Ethics Committee of the University of Extremadura (120/2018) and follows the guidelines of the Declaration of Helsinki.

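### If all three waves enter the repeated-measures ANOVA, a pupil missing in October also drops out of the June comparison between arms

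*Protocol article*

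**What the plan says.** All outcomes share one schedule. Section 2.2 states: "The variables described in Section 2.3 will be measured three times", before the programme in February, after it in June, and again as "a follow-up measure at the beginning of the following school year under the same conditions as in the two previous measures (October"). Section 2.1 agrees: "A follow-up measurement will be conducted at the beginning of the following school course (Term 3, October").

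For the analysis, Section 2.4 states that "intergroup and intragroup differences will be analysed with repeated-measures ANOVA", with nonparametric tests as the alternative where appropriate. It does not list the waves in the ANOVA, and October is not mentioned in that section. The time comparisons it does spell out have two waves. Continuous variables get "Bonferroni-corrected multiple paired" t-tests, with one of the two comparisons described as "inter-group (i.e., between the pre-test and post-test) differences". The intra-group and inter-group labels appear to be swapped there. Categorical variables get McNemar's test from baseline to post-intervention.

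Two other places bear on the point. Inclusion criterion (ii) in Section 2.1.3 requires pupils to complete the study questionnaires and names no wave. The Discussion, contribution (iv), presents evaluation of longer-term effectiveness through follow-up as one of the study's contributions. The only allowance for loss is in Section 2.1: "The minimum sample size (considering a 10% non-response) will be 345 students".

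**The concern.** Classical repeated-measures ANOVA needs a complete row per pupil. With February, June and October as the within-pupil factor, one missing wave removes the whole pupil. The October wave comes after the summer and a change of grade, so it is the wave at which pupils are most likely to have moved away, though the document gives no figure for this. A pupil with valid February and June scores would then be excluded from the June arm-by-time contrast because of something that happened after June.

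That contrast is the programme's immediate effect on the primary outcome, change in motivation for out-of-school activity. The certain cost is precision. The possible cost is bias, if the pupils lost by October differ in their June response and do so differently in the two arms. The problem comes from the named method, so it would arise even if inclusion criterion (ii) were meant for baseline alone.

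**Working it through.** **Inputs from the document.** Three waves (Sections 2.1 and 2.2); repeated-measures ANOVA (Section 2.4); minimum sample 345 (Section 2.1). The figure of 345 does not follow from the stated formula with a 3% margin: with a proportion of 0.5 that gives 1.96² × 0.25 / 0.03² = 1067, or about 810 with a finite-population correction for 3350 pupils. This does not affect the present point. I use 345 only as a scale, and the percentage rise in standard error does not depend on it.

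**Input not in the document.** The fraction d of pupils with February and June scores but no October score. I assume a range of 5% to 20%.

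**Precision.** Starting from 345 pupils with February and June data:
- complete triples = 345 × (1 − d)
- June results lost = 345 × d
- standard error multiplied by 1/√(1 − d)

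| October loss d | Complete triples | June results lost | Rise in standard error |
|---|---|---|---|
| 5% | 328 | 17 | 2.6% |
| 10% | 310 | 34 | 5.4% |
| 15% | 293 | 52 | 8.5% |
| 20% | 276 | 69 | 11.8% |

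**Bias.** This was a large-sample simulation of the February-to-June change, experimental minus control. Assumptions: SD 1 at each wave, correlation 0.6 between waves, true June effect 0.30, pupils with lower June scores more likely to be lost where loss depends on the score. The table gives the June contrast in pupils who also have October data.

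| How October loss arises | 5% loss | 10% loss | 20% loss |
|---|---|---|---|
| At random | 0.30 | 0.30 | 0.30 |
| Depends on June score, same in both arms | 0.296 | 0.291 | 0.285 |
| Depends on June score, experimental arm only | 0.319 | 0.337 | 0.370 |

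Against 0.30, the second row is low by 0.004 to 0.015 and the third is high by 0.019 to 0.070. In the third row the arms lost nearly equal proportions (10.3% and 9.8% in the 10% case). What differs is which pupils are lost, so similar attrition rates would not rule this bias out.

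**Whether another named test fills the gap.** The paired t-tests compare a pupil with himself or herself and give no between-arm estimate of change. A Kruskal-Wallis test on June scores would keep the October absentees and compare arms, but it ignores baseline and is offered only as the nonparametric alternative. McNemar's test as described is for categorical variables and works within each arm. None replaces the June arm-by-time contrast.

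**The case against.** The strongest reply is that the article never commits to a three-wave ANOVA. The contrasts it spells out are pre/post, and a February-June ANOVA with October handled separately would fit the wording and lose no June data. This stands, and it is why the point is conditional. Three waves remain the natural reading, since every outcome is measured three times, longer-term follow-up is a declared contribution, and no other method is named for October.

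A reader might infer that the plan as a whole estimates the June effect only in pupils who stay. The document does not support that: the pre/post paired tests, and a Kruskal-Wallis test at June, need no October record.

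A reader might also infer that the June effect will be overstated. No attrition rate or pattern is given, and the direction and size of any bias depend on both. The single 10% non-response allowance is not tied to a wave, so applying it to October, or to each wave in turn, is an assumption.

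Finally, handling of missing data is commonly left to an analysis plan or full protocol, neither of which is shown, and imputation before the ANOVA is not excluded. The absence of a missing-data policy is therefore no finding. What remains is the choice of a method that in its standard form needs complete triples, when a standard alternative keeps partial records.

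**Conclusion.** The point holds conditionally. If all three waves enter the ANOVA in its classical form, October loss removes valid June results from the between-arm comparison, and no other named test gives that comparison adjusted for baseline. Under an assumed October loss of 5% to 20%, the cost is about 17 to 69 of 345 June results and a standard error about 3% to 12% larger. Bias is nil under random loss and small where loss depends on the June score alike in both arms. It becomes material only where the pattern differs by arm, reaching 0.07 SD in the most adverse simulated case. The loss range and the simulation settings are assumptions. The change is worth making because it is cheap and removes the dependence of the June result on October attendance.

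**What to change.** In Section 2.4, for continuous outcomes, replace the repeated-measures ANOVA with a likelihood-based linear mixed model fitted to all available waves: arm, wave and arm-by-wave as fixed effects, a pupil random effect, and school accounted for by a method suited to only six schools. Take the June and October arm contrasts from this model. In Section 2.1.3, state that inclusion criterion (ii) does not require completion at every wave; otherwise the criterion would reintroduce the same exclusion. As a check, repeat the June contrast in all pupils with February and June data, whether or not they were seen in October.

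The cost is wording in two sections. No new data are needed and standard software suffices. The one downside is small: the model assumes that missingness is explained by the observed scores, which is a weaker assumption than the complete-case ANOVA makes.

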Given that there is no set duration as the benchmark for an intervention programme to be effective, it was decided to set a duration that was in line with previous programmes carried out in primary education [36,40,41,42]. The intervention programme for promoting motivation and PA in primary schools will be carried out over approximately 4 months (March to June). During this period, the strategies that were co-created jointly with the PE teachers in the schools that form part of the experimental group will be developed. Approximately 10 strategies are expected to be developed to involve different agents (teachers, families, and peers) both in the school and in the out-of-school context. For instance, some possible strategies are introducing new physical-sports activities or sports modalities during free time, sharing the PA carried out outside the school context with the class, involving the families, organising complementary and extracurricular activities that encourage the practice of PA, etc. In this sense, each strategy will be associated with promoting a specific BPN, assuming that each one can favour at least one BPN. The reason for designing these strategies is to ensure that the students acquire a level of autonomy that determines when, how and why to do PA and adequate competence to manage the surrounding environment, face new challenges and acquire specific skills. Moreover, this sporting practice can be performed in the company of friends and family to generate a broader social bond, using PA as a nexus of union between people who intend to practice physical sports activities with other people for greater enjoyment. Each experimental school will carry out the same strategies. However, each teacher will be able to apply them as they see fit, adapting them to their own educational reality, under the supervision of a member of the research team (see Figure 2).

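### Six schools are allocated, but section 2.4 compares the arms with pupil-level tests that have no school term; if the ICC of change is 0.01 to 0.05 (assumed), the type I error is about 12% to 32%, not 5%

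*Protocol article*

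**What the plan says.** Section 2.1 makes the school the unit of allocation: "Convenience sampling will be conducted in six different Primary Schools", and then "Three schools will be randomly assigned to the control school and the other three schools to the experimental school". The same section sets the number of pupils: "The minimum sample size (considering a 10% non-response) will be 345 students". It gives no ICC and no design effect.

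Section 2.2 has PE teachers deliver the strategies within their own schools. All experimental schools share one set of strategies, but "each teacher will be able to apply them as they see fit, adapting them to their own educational reality". The conclusions section repeats that implementation may differ between schools.

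Section 2.4 makes change in motivation for out-of-school physical activity the primary outcome. On the comparison it says that "intergroup and intragroup differences will be analysed with repeated-measures ANOVA" or by nonparametric tests such as McNemar or Kruskal-Wallis. Bonferroni-corrected t-tests follow for continuous variables and chi-square tests for categorical ones, all at p < 0.05. Results are to be described by partial eta squared and Cramer's V. The only reference to correlated observations is that "the principles of independence, normality, linearity and variance of the study variables will be tested for general linear model analyses". No school or class effect, mixed model, generalised estimating equation or cluster-robust standard error is named.

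**The concern.** Pupils in one school share the allocation, the PE teacher or teachers, the local version of the strategies and the setting. Their changes over the four months are likely to be more alike than those of pupils from different schools. The plan itself supplies a reason, since it lets each teacher adapt the strategies.

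The named tests treat every pupil as an independent unit. Ordinary school-to-school variation in change is then counted as evidence for or against the intervention, and with three schools per arm it does not average out. Testing independence does not solve this. The dependence comes from the design, six schools carry little information about a small correlation, and the plan names no action if the check fails.

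At stake is the primary between-arm p-value, the main evidence of effect. The between-arm standard error behind it is affected, and so is the reading of partial eta squared.

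**Working it through.** **Inputs from the protocol.** Six schools, 3 v 3 (section 2.1); at least 345 pupils (section 2.1); significance level 0.05 (section 2.4), taken as two-sided because the text does not say; two main time points, February and June, plus October (sections 2.1 and 2.2).

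**Input not in the protocol.** The ICC. It is assumed below and varied from 0.005 to 0.10. Because the primary outcome is change, the relevant ICC is that of the change: the share of its variance due to schools changing by different amounts.

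**The plan's own figure.** The 345 is used here only to obtain a cluster size, and it does not reproduce from the stated inputs. With p = 0.5 (assumed) and e = 3%, 1.96² × 0.25 / 0.03² = 1067. A finite-population correction for 3350 pupils brings this to 809, and 10% non-response raises it to 900. With e = 5% and the correction the result is 344.7, so 345, but without the non-response allowance. That is a separate matter. No version contains an allowance for clustering.

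**Cluster size and degrees of freedom.** m = 345 / 6 = 57.5 pupils per school. Between-arm degrees of freedom are 345 − 2 = 343 if pupils are the unit, and 6 − 2 = 4 if schools are.

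**Formulas.** Design effect DE = 1 + (m − 1) × ICC. The true standard error is √DE times the naive one. Type I error = 2 × [1 − Φ(1.96 / √DE)]. Effective sample size = 345 / DE.

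| Assumed ICC of change | DE | √DE | Type I error | Effective n |
|---|---|---|---|---|
| 0.005 | 1.282 | 1.132 | 8.4% | 269 |
| 0.01 | 1.565 | 1.251 | 11.7% | 220 |
| 0.02 | 2.130 | 1.459 | 17.9% | 162 |
| 0.05 | 3.825 | 1.956 | 31.6% | 90 |
| 0.10 | 6.650 | 2.579 | 44.7% | 52 |

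If 345 is the number before a 10% loss, about 310 pupils remain, or 51.7 per school. The error at ICC 0.01, 0.02 and 0.05 is then 11.0%, 16.7% and 29.7%. The conclusion does not depend on this choice.

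**Simulation check.** Six schools of 58 pupils, no intervention effect, 4000 runs per scenario, percentage of runs with p < 0.05:

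| Scenario | Group-by-time, 2 time points | Group-by-time, 3 time points | Plain post-test t-test | School-mean changes, t on 4 df |
|---|---|---|---|---|
| ICC of change 0.01 | 11.7% | 15.1% | 14.7% | 5.4% |
| ICC of change 0.02 | 17.9% | 23.9% | 22.4% | 5.3% |
| ICC of change 0.05 | 32.1% | 46.3% | 39.0% | 4.7% |
| Stable school difference only (ICC 0.05, no school-by-time variation) | 4.8% | 5.3% | 31.1% | 5.6% |

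The first three scenarios also contain a stable school difference of the same ICC. The last row shows which component matters. A constant level difference between schools cancels from the group-by-time test but not from a comparison of post-test scores.

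**The case against.** Four arguments can be made for the plan.

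- **The plan lists independence as an assumption and chooses tests as appropriate.** It does. But the stated choice is between ANOVA and nonparametric tests, and Kruskal-Wallis also needs independent observations. Nothing named handles clustering.
- **Such detail belongs in an analysis plan that is not shown.** That would answer an article that left the method open. This one names the tests, and those tests do not fit the allocation it describes.
- **The repeated-measures structure already removes school differences.** This stands in part. It removes stable differences, as the last simulation row shows, so not every school difference inflates the primary test. It does not remove differences in how much schools change, which local adaptation makes plausible.
- **The size is not known.** This stands. A reader might infer that the false-positive rate of this trial is 12% to 32%. The documents do not support that: they give no ICC, and the figure is 5.7% at an ICC of 0.001 and 44.7% at 0.10.

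A reader might also infer that the plan's confidence intervals are too narrow. Section 2.4 plans none. The only confidence level in the protocol belongs to the sample-size formula. The criticism reaches between-arm standard errors and p-values, and intervals only if someone derives them from those standard errors.

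**Conclusion.** The point holds in conditional form. Schools are allocated, the named between-arm tests have no school term, and the independence check leads nowhere if it fails. For any positive school-level correlation in change, the between-arm test exceeds its stated 5%. This is an error in what the plan specifies, not a missing detail.

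The size rests on assumptions: a two-sided test, about 57.5 pupils in each of six equal schools, and an ICC of the change of 0.01, 0.02 or 0.05. On those, the type I error between two time points is about 12%, 18% or 32%, and with three time points about 15%, 24% or 46%. A nominal 95% interval built on the pupil-level standard error would cover about 88%, 82% or 68%. If schools differed only by a constant level, the group-by-time test would stay near 5%, while a plain post-test comparison would still be inflated.

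**What to change.** In section 2.4, make the primary between-arm analysis a two-stage school-level analysis. Compute each school's mean change, or its baseline-adjusted mean, and compare the three values per arm by a t-test on 4 degrees of freedom (critical value 2.776). In simulation, the t-test on school-mean changes held 4.7% to 5.6%. State that the unit of inference is the school, so that the independence check no longer decides the method.

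Two mixed models are acceptable alternatives, each with Kenward-Roger or Satterthwaite degrees of freedom:

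- a pre/post model with a random school-by-time effect; or
- a model with baseline as covariate, only post-baseline scores as outcomes and a random school effect, adding school-by-time if June and October are modelled together.

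Random school and pupil intercepts alone are not enough in a pre/post model, because the school intercept cancels from the arm-by-time contrast. In one simulated data set, such a model without a baseline covariate gave the same standard error as the naive change test (0.1020 in both).

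A school-level permutation test should not stand alone. There are C(6,3) = 20 allocations, so the smallest two-sided p is 2/20 = 0.10.

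**Cost.** Analysis wording only; no new data. The price is precision. In units of the pupil SD of change, the naive 95% half-width is 1.96 × √(2/172.5) = 0.21. The school-level half-width is about 2.776 × √(2/3) × √(DE/57.5), which is 0.37 at ICC 0.01 and 0.58 at ICC 0.05. That is what three schools per arm can support under those assumptions.
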